**Methods:**

iPHORECAST has a multicentre, prospective, randomised, open-label, blinded endpoint (PROBE) design. Presymptomatic PLN p.Arg14del carriers are randomised to receive either 50 mg eplerenone once daily or no treatment. The primary endpoint of the study is a multiparametric assessment of disease progression including cardiac magnetic resonance parameters (left and right ventricular volumes, systolic function and fibrosis), electrocardiographic parameters (QRS voltage, ventricular ectopy), signs and/or symptoms related to DCM and ACM, and cardiovascular death. The follow-up duration is set at 3 years.

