### Design

This outpatient study is a multicentre, prospective, randomised trial with blinded assessment of endpoints design (PROBE) [20]. The participating centres are the University Medical Center Groningen (which is the coordinating centre and CMR core lab); Amsterdam University Medical Center; Antonius Hospital Sneek and University Medical Center Utrecht. Carriers were randomly assigned to one of the two study arms, either eplerenone or control (no treatment), in a 1:1 ratio. The follow-up period is 3 years (see the section *Study endpoints*).

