### Study endpoints

The primary and secondary endpoints are listed in Tab. 3. The primary endpoint is a multiparametric assessment of disease progression defined as a responder-based composite primary endpoint (Tab. 3). If one of the predefined parameters of the composite primary endpoint is reached, CMR imaging is performed and study end date recorded. After a follow-up period of 3 years, outcomes will be assessed by an independent adjudication committee blinded to the allocated group. In case of a favourable trend (but no significant effect as yet), the DSMB may advise continuing the study for 2 more years (“adaptive design”).

**Table 3 Tab3:** Primary and secondary endpoints

*Primary endpoint*^a^
LV end-diastolic volume, increase > 10% (assessed with CMR)
LV ejection fraction, absolute decrease > 5% (assessed with CMR)
RV end-diastolic volume, increase > 10% (assessed with CMR)
RV ejection fraction, absolute decrease > 5% (assessed with CMR)
Late enhancement, absolute increase > 5% (assessed with CMR)
QRS voltage, decrease > 25% (ECG, measured in I, II and III in mV)
Occurrence of non-sustained ventricular tachycardia (Holter monitoring, exercise testing)
Heart failure signs and/or symptoms or arrhythmias necessitating medical treatment according to the guidelines and likely due to arrhythmogenic cardiomyopathy
*Secondary endpoints*
All individual components of the primary endpoint
Diagnosis of DCM (according to Mestroni criteria [19])
Diagnosis of ARVC (according to revised task force criteria [18])
Development of global or regional dysfunction and structural alterations (according to revised task force criterion 1 [18])
QRS axis (12-lead ECG)
Conduction intervals (PR interval, QRS duration [12-lead ECG; SA-ECG])
STT segment changes (12-lead ECG)
Change in biomarkers
Occurrence of sustained ventricular tachycardia or ventricular fibrillation
Hospitalisation for a cardiovascular reason

*LV* left ventricular, *CMR* cardiac magnetic resonance*, RV* right ventricular,* ECG* electrocardiogram,* DCM* dilated cardiomyopathy, *ARVC* arrhythmogenic right ventricular cardiomyopathy,* SA-ECG* signal-averaged electrocardiography

^a^The primary endpoint is a multiparametric assessment of disease progression defined as a responder-based composite primary endpoint. If one of the predefined parameters of the composite primary endpoint is reached, CMR imaging is performed and study end date recorded

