### Sample size estimation

This clinical trial was designed based on the assumptions that 50% of the presymptomatic PLN p.Arg14del carrier group without treatment will reach the primary endpoint within 3 years and that treatment with eplerenone is expected to reduce this percentage by 50%. To ensure at least 80% power to detect a difference between the control group and the eplerenone group, at a significance level of 0.05, 128 carriers (64 in each group) are needed. To account for 10–15% loss to follow-up during the study, we aimed to include 150 subjects.

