### Study organisation and monitoring

This is an investigator-initiated study organised by the executive steering committee, which is based in the Department of Cardiology, University Medical Center Groningen, Groningen, the Netherlands. The executive steering committee is responsible for overall supervision of the study, policy decisions, protocol amendments, publications and presentations. An independent DSMB monitors the overall conduct of this study by receiving and reviewing reports of serious adverse events, reviewing periodic reports of safety data and establishing ‘stopping rules’ for the trial for safety reasons only.

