### Statistical analysis

After completion of the study, all eligible carriers who have been randomised to the treatment arm and received at least 1 dose of eplerenone will be used in the analyses of the primary and secondary efficacy endpoints, as well as in the safety analysis. Safety will be assessed by summarising the incidence and type of adverse events and the changes in laboratory parameters. The proportion of carriers experiencing serious adverse events and the proportion of carriers with noteworthy changes in laboratory parameters will be compared between treatment groups. The analysis of primary endpoints and secondary endpoints will be performed according to their assigned treatment group in accordance with the intention-to-treat principle. Additional analysis sets may be used in exploratory analyses. The number of subjects withdrawing from the study will be tabulated by their reasons for withdrawal and by treatment group. Potenzial biases due to withdrawal of subjects will be investigated. Baseline characteristics will be compared using chi-squared test (or Fisher’s exact test if appropriate). If differences are found, caution will be exercised when interpreting the results of the analyses between groups and methods may be modified to adjust for this difference.

The primary outcome will be presented by Kaplan-Meier curves for the treatment group, followed by the stratified log-rank test using stratification variables. Multivariate analysis will also be used to compare the endpoints between the two groups, adjusting for other variables including sex, age and screening centre. For missing data, the last observations made will be used. Unless stated otherwise, all secondary analyses will be performed using the same subjects included in the primary analysis. Secondary variables will be analysed using an appropriate statistical test, depending on the nature of the variable. Changes in parameters over time in the different treatment groups will be analysed using repeated measurement analysis or techniques that evaluate the timing of endpoints, when appropriate. For all tests, a *p*-value < 0.05 is considered statistically significant. Statistical analysis will be performed in SPSS (IBM SPSS Inc., Chicago, IL, USA; newest version at moment of analysis).

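### The option to extend by 2 years after a favourable but non-significant 3-year result implies a second test with no alpha set aside, raising the two-sided error from 5% to about 5.5–6.5%

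*Protocol article*

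**What the plan says.** - **Extension.** Study endpoints, after describing adjudication at 3 years: "In case of a favourable trend (but no significant effect as yet), the DSMB may advise continuing the study for 2 more years". The article labels this adaptive. It does not define a favourable trend.
- **Significance level.** Statistical analysis: "For all tests, a *p*-value < 0.05 is considered statistically significant". Sample size estimation: "To ensure at least 80% power to detect a difference between the control group and the eplerenone group", and "at a significance level of 0.05, 128 carriers (64 in each group) are needed".
- **Follow-up.** Abstract, Methods: "The follow-up duration is set at 3 years". Design: "The follow-up period is 3 years". The Treatment section and Table 2 place CMR at the start and at 36 months, and Table 2 ends at year 3.
- **DSMB.** Study organisation and monitoring lists review of serious adverse event reports, review of periodic safety data, and the setting of stopping rules "for the trial for safety reasons only". That section and Ethical considerations also give the DSMB oversight of the trial's overall conduct.
- **Amendment.** Baseline results reports that inclusion stopped in January 2018 at 84 participants, that they would complete the planned follow-up, and that the dichotomous composite gave way to its components on a continuous scale. The analysis plan was amended accordingly. The extension clause is not mentioned.

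**The concern.** The clause makes sense only if significance is judged at 3 years and, when it is missed in the hoped-for direction, judged again at 5 years. If both judgements use 0.05, the procedure as a whole does not keep its stated 5% level, and nearly all of the excess is false claims of benefit. With 84 participants instead of the 128 called for, a favourable but non-significant 3-year result is a realistic outcome, so the condition that opens the option could well be met.

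The clause also sits awkwardly with the rest of the article. It has the DSMB act on a between-arm efficacy trend, although no efficacy review is among its listed tasks. Five of the eight primary components in Table 3 are CMR measurements, and none is scheduled after 36 months.

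**Working it through.** **1. The plan's own figure: is the whole 0.05 spent on one comparison?** Inputs from Sample size estimation: 50% of controls reach the endpoint within 3 years, halved to 25% on eplerenone, level 0.05, power at least 80%. Exact power of the two-sided Fisher test is 79.4% at 63 per group and 80.2% at 64, so 64 per group (128) is reproduced. For dropout, 128/0.90 = 142.2 and 128/0.85 = 150.6, consistent with the target of 150. One comparison at the full 0.05 yields the stated size; nothing is reserved for a later test.

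**2. Share of the 5-year information available at 3 years (t).** The article does not give it. Assume constant hazards and the composite endpoint used before the amendment. Under the null with 50% events at 3 years in both arms:

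- 5-year event rate = 1 − 0.5^(5/3) = 0.685
- t = 0.50/0.685 = 0.73

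A null rate of 37.5% gives 0.375/0.543 = 0.69, and 25% gives 0.25/0.381 = 0.66. The range 0.6–0.8 covers these.

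**3. Overall error.** Let Z3 and Z5 be the test statistics at 3 and 5 years, positive for benefit, with correlation √t under the null. Let k be the trend above which the trial is extended.

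- Two-sided error = P(|Z3| > 1.96) + P(k < Z3 ≤ 1.96 and |Z5| > 1.96)
- False-benefit error = P(Z3 > 1.96) + P(k < Z3 ≤ 1.96 and Z5 > 1.96)

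The first terms are 0.05 and 0.025. The second terms are the excess and cannot be negative. Because the trigger is undefined, k is varied. Entries are two-sided error / false-benefit error:

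| t | any Z3 > 0 | one-sided p < 0.10 | one-sided p < 0.05 |
|---|---|---|---|
| 0.60 | 6.5% / 4.0% | 5.9% / 3.4% | 5.5% / 3.0% |
| 0.73 | 6.2% / 3.7% | 5.9% / 3.4% | 5.5% / 3.0% |
| 0.80 | 6.0% / 3.5% | 5.9% / 3.4% | 5.5% / 3.0% |

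**4. Check by simulation.** Log-rank tests on exponential data under the null, extension whenever Z3 > 0, 40,000 runs per setting: 6.4% / 3.9% for 128 participants with 50% events at 3 years; 6.3% / 3.8% for 84 participants with 50%; 6.3% / 3.8% for 128 with 37.5%. These agree with the first column.

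**5. What a confirmatory 5-year test would cost.** Using the same level at both looks and holding 0.05 overall, each test gets about 0.033 at t = 0.73 (0.031–0.035 over t = 0.60–0.80). O'Brien-Fleming-type spending at t = 0.70 leaves about 0.015 two-sided at 3 years. If the 3-year test keeps the full 0.05, nothing is left for 5 years.

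**The case against.** The strongest reply is that the 2018 amendment has overtaken the clause. The article says the cohort will complete its planned follow-up, and the remaining participants are expected to finish in 2021, which is January 2018 plus 3 years. Nothing there plans an extension, so this may be a leftover sentence. That stands as a limit on how much is at stake, but the clause is in the current text and nothing withdraws it.

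Alpha handling is also commonly left to the analysis plan, which is not shown. Silence would therefore be no fault. But the article is not silent: it fixes an efficacy-triggered extension and a flat 0.05 for all tests.

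Three stronger readings are tempting and are not supported:

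- **That the clause contradicts a safety-only DSMB remit.** The safety restriction qualifies the stopping rules, and extending is not stopping. The DSMB also oversees overall conduct and supported the 2018 change of design. What can be said is that its listed tasks include no efficacy review.
- **That a 5-year result would rest on a cohort that had largely left.** Entry from May 2014 to January 2018 spans 44 months, but the article does not say when the DSMB would decide. It describes all investigations except blood analysis as routine care, so later data may exist.
- **That the error is 6.0–6.5%.** This holds only if every positive trend leads to extension. The text speaks of a favourable trend and of advice that may be given. Stricter triggers give 5.5–5.9%, and less again if the option is not always taken up.

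**Conclusion.** The point holds, at moderate size. As written, the rule allows a second test after a failed test at full level, and the overall two-sided error becomes about 5.5–6.5% instead of 5%, with false-benefit error about 3.0–4.0% instead of 2.5%. These figures assume two-sided testing (the article does not state sidedness), t of 0.6–0.8, a trigger between Z3 > 0 and one-sided p < 0.05, and extension whenever the trigger is met.

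They describe the composite endpoint. An event-based t does not carry over to components analysed on a continuous scale, so the size for the amended analysis cannot be derived from the article. The direction does carry over: retesting at 0.05 only after a favourable miss adds rejections unless the two statistics are identical. Whether the clause is still in force is itself unclear and needs an answer.

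**What to change.** Delete the extension clause from Study endpoints. Alternatively, keep the option but add one sentence: the 36-month analysis at two-sided 0.05 is the only confirmatory test, and any longer follow-up is exploratory. Either way, reconcile Study endpoints, Study organisation and monitoring, and Baseline results, so that it is clear whether the clause survived the 2018 amendment and whether the DSMB reviews efficacy by arm.

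The wording costs almost nothing. The real price is that the sponsor gives up a second chance at significance, which will be felt with 84 participants instead of 128.

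If a confirmatory 5-year test is kept, more is needed: a defined trigger, an alpha split fixed beforehand, a written efficacy remit for the DSMB, and scheduled endpoint measurements after 36 months. The split lowers the level at 3 years to about 0.033 with equal levels, or about 0.015 with O'Brien-Fleming-type spending at t = 0.70, a loss of power in a trial already short of its target.

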### Sample size estimation

This clinical trial was designed based on the assumptions that 50% of the presymptomatic PLN p.Arg14del carrier group without treatment will reach the primary endpoint within 3 years and that treatment with eplerenone is expected to reduce this percentage by 50%. To ensure at least 80% power to detect a difference between the control group and the eplerenone group, at a significance level of 0.05, 128 carriers (64 in each group) are needed. To account for 10–15% loss to follow-up during the study, we aimed to include 150 subjects.

### Randomisation and blinding

Central randomisation was conducted by the Trial Coordination Center of the University Medical Center Groningen (www.tcc.umcg.nl). Randomisation was stratified according to participating centres to ensure a similar sample distribution between the two test groups. According to the PROBE design, randomisation is blinded to the CMR core lab in the UMCG for assessment of the CMR images, which are performed as previously described [9]. An independent endpoint adjudication committee assesses the other primary and secondary endpoints.

### Study organisation and monitoring

This is an investigator-initiated study organised by the executive steering committee, which is based in the Department of Cardiology, University Medical Center Groningen, Groningen, the Netherlands. The executive steering committee is responsible for overall supervision of the study, policy decisions, protocol amendments, publications and presentations. An independent DSMB monitors the overall conduct of this study by receiving and reviewing reports of serious adverse events, reviewing periodic reports of safety data and establishing ‘stopping rules’ for the trial for safety reasons only.

### Biomarkers

Venous blood samples from all participants are stored and analysed for levels of biomarkers of fibrosis [21] and for biomarkers of apoptosis, haemodynamic status and inflammation. We will investigate whether these biomarkers predict disease progression. In addition to the volume of blood needed to measure these biomarkers, additional blood (serum and plasma) is taken and stored to allow for additional analyses in the future (samples stored for a maximum of 15 years). The amount of blood taken per venipuncture is 20 ml (at the start of the study and after 3 years). Carriers were asked to give their written informed consent for these additional analyses at the start of the study.

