### Treatment

In the treatment arm, eplerenone was initiated on the day of randomisation at 50 mg orally once daily. The dose of 50 mg once daily is the recommended dose in patients with heart failure. Carriers are maintained at this target dose, or the maximum tolerated dose, until the end of the study. Serum potassium and estimated glomerular filtration rate (eGRF) are monitored at the start of the study, 1–2 week(s) after study start and yearly, and these measures are documented together with the other investigations and vital parameters. The dose is reduced if needed, i.e. in case of hyperkalaemia (serum potassium > 5.5 mmol/l). Carriers undergo yearly follow-up in the cardiology outpatient clinic at each participating centre following routine clinical care. Physical examination, blood sampling (when treated with eplerenone), electrocardiogram, Holter monitoring and ergometry are performed every 12 months. CMR imaging and SA-ECG are performed at the start and end (36 months) of the study (Tab. 2).

**Table 2 Tab2:** Overview of study procedures

	Visit 1 start	Visit 2 1 week	Visit 3 1 year	Visit 4 2 years	Visit 5 3 years
Visit to outpatient clinic	*✔*	**–**	*✔*	*✔*	*✔*
History and current status	*✔*	**–**	*✔*	*✔*	*✔*
Physical examination	*✔*	**–**	*✔*	*✔*	*✔*
Electrocardiogram	*✔*	–	*✔*	*✔*	*✔*
Echocardiogram	*✔*	–	*✔*	*✔*	*✔*
Holter monitoring	*✔*	–	*✔*	*✔*	*✔*
Ergometry	*✔*	–	*✔*	*✔*	*✔*
Signal-averaged ECG	*✔*	–	–	–	*✔*
CMR	*✔*	–	–	–	*✔*
Blood analysis	*✔*	*✔*^a^	*✔*^a^	*✔*^a^	*✔*

Note: Subjects undergo several investigations as summarised in this table. They are requested to visit the outpatient clinic at baseline and at 1‑year intervals thereafter. Subjects randomised to eplerenone visit the outpatient clinic or their general practitioner after 1 week to check serum potassium and eGRF, which are also checked in these subjects at the yearly visits. Of note, all investigations except blood analysis are already performed as part of routine clinical care, which routinely includes evaluation of signs and symptoms of DCM and ACM. For the purpose of the study, we collect and use these available data.

*ECG* electrocardiography, *CMR* cardiac magnetic resonance, *eGFR* estimated glomerular filtration rate, *DCM* dilated cardiomyopathy, *ACM* arrhythmogenic cardiomyopathy

^a^ only for subjects randomised to eplerenone

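### The early-end rule brings forward CMR but not the biomarker sample or SA-ECG, so participants who end early have no scheduled end measurement for two secondary endpoints

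*Protocol article*

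**What the plan says.** All references are to the protocol article.

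- **Early end.** Study endpoints and the Table 3 footnote give the same instruction for a participant who reaches one component of the composite: "CMR imaging is performed and study end date recorded". Nothing else is attached to that event.
- **Biomarker blood.** The Biomarkers section covers all participants and gives two times: "The amount of blood taken per venipuncture is 20 ml (at the start of the study and after 3 years".
- **Other blood.** The Treatment section says "blood sampling (when treated with eplerenone), electrocardiogram, Holter monitoring and ergometry are performed every 12 months". Table 2 shows blood for everyone at the start and at year 3. At 1 week, year 1 and year 2 it is for the eplerenone arm only, and the table note gives the purpose as potassium and renal function.
- **SA-ECG and CMR.** Treatment and Table 2 schedule both only at the start and at 36 months.
- **Endpoints affected.** Table 3 lists biomarker change as a secondary endpoint, and also conduction intervals, measured by 12-lead ECG and SA-ECG.
- **Missing data.** Statistical analysis says that the last observation made will be used.
- **Amendment.** Baseline results reports that inclusion stopped in January 2018 with 84 participants, that the components are now analysed on a continuous scale, and that the protocolled follow-up is to be completed. It does not say whether the early-end rule still applies.

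**The concern.** CMR, SA-ECG and biomarker blood share one schedule: start and 36 months. An early end would lose all three. The plan has a rule that rescues CMR and leaves the other two where they were. Followed to the letter, a participant whose study ends at year 1 or 2 has a baseline sample and no second one.

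The loss is not random, because progression causes it. The participants without an end value are those in whom a fibrosis marker would be most expected to move. If eplerenone works, there are more of them in the control arm. The last-observation rule then takes the only value available, the baseline one, and records no change in people known to have progressed. For an antifibrotic hypothesis, this blunts the blood-based evidence on mechanism. It also weakens any analysis that relates marker change to progression.

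**Working it through.** **1. Planning rates.** Sample size estimation sets the control rate: "50% of the presymptomatic PLN p.Arg14del carrier group without treatment will reach the primary endpoint within 3 years". Eplerenone is assumed to halve it, which, read as a relative reduction, gives 25%. The rates fit the plan's own figure: "at a significance level of 0.05, 128 carriers (64 in each group) are needed". For 50% against 25% with a two-sided Fisher exact test (sidedness assumed, as it is not stated), power is 79.4% at 63 per group and 80.2% at 64 per group. So 64 per group reaches the stated 80%, and 50% and 25% are the right inputs below.

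**2. Who can end early.** Table 3 has eight components. Five are CMR measures, scheduled only at the start and at 36 months, so by schedule they cannot trigger an early end. Three can: QRS voltage, non-sustained ventricular tachycardia, and heart failure or arrhythmia needing treatment. A participant who progresses only on the month-36 CMR is at the visit where blood and SA-ECG are also taken.

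**3. Numbers without an end sample.** Let f be the share of progressors who end before month 36. The article does not give f, so it is varied. With 42 per arm, the number affected is 42 × rate × f.

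| f | Control (42 × 0.50 × f) | Eplerenone (42 × 0.25 × f) |
|---|---|---|
| 0.25 | 5.25 | 2.6 |
| 0.50 | 10.5 | 5.25 |
| 0.75 | 15.75 | 7.9 |

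With f equal in both arms the split is 2:1 at every f. If eplerenone has no effect, the rates are equal and so is the split.

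**4. Effect on the arm difference under the stated rule.** Assume that progressors change by 1 SD and others by 0. The true mean changes are 0.50 and 0.25 SD, a difference of 0.25 SD. Carrying baseline forward sets the change to 0 in early enders, so each arm's mean is its rate × (1 − f):

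difference = 0.50(1 − f) − 0.25(1 − f) = 0.25(1 − f)

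- f = 0.25: 0.25 × 0.75 = 0.1875
- f = 0.50: 0.25 × 0.50 = 0.125
- f = 0.75: 0.25 × 0.25 = 0.0625

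The estimate is 25%, 50% or 75% too small.

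**5. For comparison, available samples only.** The plan does not state this analysis. The arm means become 0.50(1 − f)/(1 − 0.50f) and 0.25(1 − f)/(1 − 0.25f).

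- f = 0.25: 0.429 − 0.200 = 0.229
- f = 0.50: 0.333 − 0.143 = 0.190
- f = 0.75: 0.200 − 0.077 = 0.123

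Dropping the participants loses 9%, 24% or 51% of the difference. In this illustration the carry-forward rule does more harm than omission, and neither recovers the missing information.

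**The case against.** The strongest reply is that this is a condensed article. It does not say that blood is withheld at an early end, and it does not cancel the year-3 visit. An early study end could reasonably be read as bringing the whole closing visit forward, and the full protocol may say so. This stands to the extent that nobody can claim the plan forbids the sample. It does not remove the point. The article does describe what an early end triggers, twice, and names only CMR among three measures with the same schedule.

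Several stronger readings are tempting and are not supported:

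- **All progressors lack a sample.** No. Those found only by CMR at month 36 are sampled.
- **The loss falls mainly on control.** This holds only under the planning effect with equal early detection. Under no effect it is even.
- **The Treatment section contradicts Table 2 on who has blood taken.** Its sentence follows the text on potassium and renal function and can be read as safety blood, separate from the biomarker draw. A contradiction is not established.
- **Eplerenone participants have a usable interim sample that controls lack.** Nothing says that serum or plasma from the safety bloods is stored for biomarkers.

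It is also fair to say that baseline samples from everyone still serve the stated aim of predicting progression, that 12-lead conduction intervals are recorded yearly and are unaffected, and that possible bias from withdrawal is to be investigated. The last of these does not clearly cover participants who end because they reached an endpoint.

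**Conclusion.** The point holds as a gap between the early-end rule and the measurement schedule. Following the text as written, participants who end early on one of the three non-CMR components have no scheduled end value for biomarker change or for SA-ECG conduction intervals. The loss depends on progression, and the last-observation rule would turn the missing biomarker change into zero.

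The size is illustrative. A 0.25 SD difference shrinks to 0.19, 0.125 or 0.06 SD for early shares of 25%, 50% or 75%. This rests on the planning rates, an equal early share in both arms, and a 1 SD change confined to progressors. The article gives neither the early share nor the marker change. If the early share differs between arms, neither the 2:1 split nor these figures apply.

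Only secondary endpoints are affected. Most participants had finished when the article was written, so a change of procedure can help few of them and the analytic part of the remedy matters more. The 2018 amendment leaves a further uncertainty. If the early-end rule was dropped then, later participants may have gone on to month 36. Inclusion began in May 2014, however, so some year-1 and year-2 visits fell under the rule as written.

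**What to change.** 1. In Study endpoints and the Table 3 footnote, state that the planned 20 ml biomarker sample and the SA-ECG are done with the triggered CMR, in both arms, and count as that participant's end measurement.
2. Record time on study at that measurement and use it in the analysis.
3. State in Baseline results, or in the amended analysis plan, whether the early-end rule still applies after the 2018 amendment.
4. Exempt these endpoints from the last-observation rule where the only value is the baseline one. For participants who already ended early without a sample, do not use baseline as the end value.
5. Report the number of missing end samples by arm and progression status.

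The cost is a few sentences and one table. The draw and the SA-ECG are already planned and would move to the time of a CMR that the rule already requires. The small downside is that end measurements come at unequal times, which is why time on study has to enter the analysis.
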